### Software development and piloting

The objective of this phase is to develop and pilot a prototype system for electronic collection of PROMs and PREMs based upon the results of the the pre-development phase.

The ePRM system is schematically described in Fig. 2. The whole data management process (patient registration, questionnaire completion, data elaboration and clinician consultation) takes place within the hospital network. Expansion of the system allowing also for data completion by the patient from outside the hospital network will be developed in the future. Ideally, PRM triggers will come from hospital acceptance IT systems (i.e. unified booking centre system (UBCS) and admission discharge and transfer system (ADT)) (a) or from a data collection coordinator (b). Then, patients will fill in PRMs questionnaires through a dedicated interface using a tablet provided by the hospital (c); data will be elaborated (scoring and graphical presentation) by the system, and scores will be displayed on the patient interface (d). All data will be saved into a secure server within the hospital network.

**Fig. 2 Fig2:**
[figure not shown]
Patient Voices system diagram. **a** and **b** ePROM and ePREM triggers; **c** patient questionnaire completion; **d** feedback to patients; **e** individual level feedback to clinicians; **f** group level feedback clinicians; **g** administrator tasks. (ePROMs: electronic Patient Reported Outcome Measurements, ePREMs: electronic Patient Reported Experience Measurements, EMR: Electronic Medical Record)

A distinction must be drawn between ePROMs and ePREMs as regard how they are reported to clinicians. While individual ePROMs data will be available to the clinicians during the consultation, ePREM data collection should be anonymous to allow the patient freedom in expressiong judgments; for this reason only group level reporting will be available for ePREM and then ePREM system does not need to interact with the EMR. Figure 2 in fact indicates that after completion, individual ePROMs scores are real time transferred and graphically displayed into the ePROMs section of the EMR (e), in order for the clinician to consult them; both ePROMs and ePREMs will be stored and successively elaborated for group level reporting accessible to clinicians (e). Finally Fig. 2 enlights the role of the “system administrator” who operates through a dedicated dashboard to modifiy existing or to add new ePRMs tools, to authorize users to system access, to download patients data and manages group level reports (f).

Based on authors previous experiences and on indications from the literature [17, 26–28], main key features of the system will be:
ease of accessibility and usage for the patients and clinicianssecurity of patient datalinkage to other systems (EMR, appointment/scheduling, patient portal)flexibility (i.e the possibility to create questionnaires without significant programming effort)real-time and user-friendly display of ePROMs results to cliniciansmeaningful display of PREMs data for monitoring patient experience with care and for benchmarking between wards

The prototypes will be pilot tested on 5 clinicians and 10 patient advocates. Comments will be collated on: logging in, accessing the system, navigation through the questionnaire; accessing and inspection the results. Staff and patients will be interviewed (semi-structured interviews) and changes will be applied to overcome problems emerged. A new version of the prototype will be developed and used in the quantitative feasibility phase described below (Fig. 1). The system will be further refined for improvement during data collection in feasibility studies. A final version of the system will be developed at the end of data collection and elaboration.

### Feasibility assessment

The aims of this phase are:
To assess compliance, acceptability, and usability of a routine ePROMs and ePREMs assessment both by patients and health care providers.To identify patient and health care provider related barriers.To identify potential engagement strategies for the implementation of routine ePROM assessment in oncology clinical practice.

Both quantitative (studies A, B and C) and qualitative (study D) feasibility studies will be carried out:
STUDY A: a longitudinal study of symptom screening and monitoring in cancer patients attending 3 out-patient clinics of INT, namely palliative care, thoracic oncology and genito-urinary cancer clinics.STUDY B: a cross-sectional study of psychological distress screening among in-patients admitted to hematology, medical oncology and breast surgery wards of INT.STUDY C: a longitudinal study for the assessment of patient experience of care during different phases of the care process, among patients followed by multidisciplinary teams in INT, namely the Breast Cancer Unit, Prostate cancer program, Thoracic cancer Unit, Head&Neck cancer Unit, Mesenchimal cancer Unit.STUDY D: a feasibility qualitative study (interviews with patients and focus groups with HCPs) with users involved in the quantitative studies.

### Methods for quantitative feasibility studies

#### Patient population

All consecutive adult cancer patients attending one of the above out-patient clinics, in-patient wards or followed by one of the multidisciplinary team in a pre-specified time period, will be proposed to be enrolled in the study. Patients with inability to fill in the system due to cognitive impairment, psychological disturbances or language problems as judged by the study personnel upon inclusion, will not be eligible. All physicians working in the outpatient clinic in those days in which system is tested, are eligible to study participation.

#### PROMs and PREMs questionnaires

Grounded on their relevance within patient reported measures literature in oncology [18, 29–32], three PRM areas have been indentified to be addressed in the three quantitative feasibility studies: symptom burden (study A), psychological distress (study B) and patient reported experience and satisfaction with care received (study C).

Symptom burden will be measured using the Edmonton symptom assessment scale (ESAS) [33] (i.e., pain, tiredness, drowsiness, nausea, reduced appetite, breathlessness, depression, anxiety, well-being) plus sleep, constipation and vomiting. The intensity of each symptom is assessed on 0–10 numerical rating scales (higher scores indicate greater symptom severity). The ESAS instrument is one of the most widely used and with a robust psychometric documentation in various languages [33, 34] and has been validated in Italian in a sample of advanced cancer patients [35].

Psychological distress screening among in-patients will be performed using the Distress Thermometer (DT), a single-item 0–10 numerical rating scale, on which participants rate their level of distress from any cause in the preceding 7 days [36]. The DT is accompanied by a 35 item problem list, which prompts patients to identify their problems in five different categories: practical, family related, emotional, spiritual/religious, and physical. Scores of 4 or higher suggest a level of distress that has clinical significance. The DT has been validated in Italian language [37].

In the longitudinal feasibility pilot study C, questionnaires for the survey will be developed from existing instruments (the questionnaire developed in Bench-Can and EURACAN projects [38], the patient satisfaction with cancer care questionnaire [39] and the institutional customer satisfaction survey). The adaptation of the questionnaire content to the specific patient population, will be performed with the contribution of clinicians of the multidisciplinary teams involved, discussed with cancer patients’ representatives and pre-tested among a restricted group of users.

#### Data collection procedures

A trained data collection coordinator (DCC), a research nurse or a psychologist or a physician, will perform eligibility screening, propose the patient to be enrolled in the study, collect written informed consent and provide basic training in how to use the device. The DCC will also be available for any help the patient may need during the compilation. At the end of the compilation, system usability as perceived by patient will be collected and the following data will be registered by the DCC: reason for potential incompleteness, amount of assistance needed and system usability. The system will automatically register clinician access to patients’ data. System usability as perceived by clinicians will be collected at the end of study period.

Patients attending the out-patient clinics involved in Study A, will fill in the symptom burden questionnaire at the first 3 visit performed during the study period, while symptom distress screening among in-patients (Study B) will be performed on admission.

In Study C questionnaires will be filled-in along the care pathway at the following clinically relevant points: T0 (at diagnosis), T1 (first treatment decision making step), T2 (end of active treatment), T3 (disease progression), T4 (follow-up). Exact timing of T0 to T4 will be different for the five multidisciplinary team Units involved and the maximum follow-up time will not exceed 6 months from enrollment.

#### Study endpoints

The main study endpoints are the rates of compliance with the system at baseline assessment by both patient (percent of eligible patients completing electronic questionnaires) and physicians (percent of clinical encounters in which the physician gets access to data provided by ePROM) (the latter only in studies A and B).

Secondary endpoints are:
proportion of eligible patients among those screened;proportion of patients refusing to use the system and reasons for refusal;proportion of patients filling in the system without external help;average proportion of missing items for each compilation;average time to fill in the system;average level of perceived system usability by patients;average level of perceived system usability by physicians;identification of features of the system which need refinement.

Additional secondary endpoints in the longitudinal feasibility studies:
rate of drop-out during the longitudinal assessment and reasons for drop-out;rate of intermittent missing assessment and reasons for missingness;clinician perception about the usefulness of PROMs for treatment decisions.

#### Assessment methods

A paper and pencil self-report form will be used to gather patients’ education level and acquaintance/experience with e-devices (smartphones, tablets, computers). Patients’ basic demographic and clinical data (sex, date of birth, tumor site, stage of the disease, pain and other symptom medication prescription) will be gathered from the EMR. Time needed to complete data collection for each patient will be registered by the system. Data regarding gender, years of experience in oncology practice and experience with e-devices, will be collected also for the clinicians participating in the study. After testing, patients and clinicians will fill out the System Usability Scale (SUS), a standardized questionnaire used to assess participants’ perceptions of system usability [29]. The SUS is made up of 10 items rated on a 5-point Likert scale and its final score is a summated rating scale ranging from 0 to 100 after resacaling. An open ended question will also be asked to all participants in order to assess whether any of the system features were difficulty to use or for which they propose modifications.

#### Sample size and data analysis

Six hundred consecutive cancer patients will be enrolled (200 in each of studies A, B, and C).

In the hypothesis that the percentage of successful assessments/consultation (“rate of compliance” among patients and clinicians) is 50% (hypothesis of maximum variability, and then maximum imprecision), a sample size of 200 allows the estimation of a 95% CI for the rate of compliance with a precision (half width) of 6.9% [23].

Basic descriptive statistics will be applied to characterize the study sample. Point and interval estimates (95% CI) of rates and averages described in primary and secondary endpoints, will be calculated for the whole sample and by outpatient clinic/inhospital ward. The association between patient related characteristics and binary as well as continuous outcomes will be respectively analyzed with logistic and linear regression models.

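### The 6.9% half width holds for patient compliance, but it is too optimistic for physician compliance in Studies A and B, where encounters are nested within physicians

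*Protocol article*

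**What the plan says.** Under Study endpoints there are two main endpoints: "The main study endpoints are the rates of compliance with the system at baseline assessment", one for patients and one for physicians. The patient rate counts eligible patients who complete the electronic questionnaires. The physician rate is the "percent of clinical encounters in which the physician gets access to data provided by ePROM", and applies to Studies A and B only.

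Under Sample size and data analysis, "Six hundred consecutive cancer patients will be enrolled (200 in each of studies A, B, and C"). A single hypothesis then covers both rates: compliance "among patients and clinicians) is 50% (hypothesis of maximum variability, and then maximum imprecision"). From it the protocol concludes that "a sample size of 200 allows the estimation of a 95% CI for the rate of compliance with a precision (half width) of 6.9" percent. The same section plans 95% confidence intervals for the whole sample and by clinic or ward.

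Feasibility assessment draws Study A from three outpatient clinics and Study B from three wards, all at one institute. On physicians, Patient population says only that "All physicians working in the outpatient clinic in those days in which system is tested" are eligible. The protocol gives no number of physicians, ICC or design effect.

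**The concern.** For patient compliance the unit is the patient, each contributing one baseline result, so 200 patients can reasonably be treated as 200 independent observations. For physician compliance the unit is the encounter, and the same physician will normally account for several. If some physicians tend to open the ePROM section and others do not, encounters of the same physician resemble each other and carry less information than the same number of independent ones. The protocol itself allows that clinicians may differ: Assessment methods records their years of oncology experience and their experience with electronic devices.

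Choosing 50% maximises the binomial variance, but it does not bound the extra variance from clustering. The 6.9 points is therefore not a worst case for the physician endpoint, although the protocol presents it as one.

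Physician uptake is one of the two main endpoints. The Discussion names insufficient clinician engagement as a way the project could fall short, and the feasibility results go to the stakeholder team that will design implementation. An interval that is too narrow would overstate how well uptake is known. The problem is sharper by clinic or ward: with 200/3, or about 67 encounters each, one or two physicians could drive the rate.

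**Working it through.** **Inputs from the protocol.** n = 200 per study, p = 0.50, 95% confidence, stated half width 6.9% (Sample size and data analysis); unit of the physician endpoint = encounter, at baseline, so about one per patient (Study endpoints).

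**Inputs assumed, because the protocol does not give them.** Number of physicians per study, k = 6 to 40. Within-physician ICC of access, 0.01 to 0.30. Encounters spread equally, so m = 200/k per physician.

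**Step 1: reproduce the stated figure.**
Half width = 1.96 × √(p(1 − p)/n) = 1.96 × √(0.25/200) = 0.0693, or 6.9 points. Other single-sample intervals give nearly the same: Wilson 6.86, Clopper-Pearson 7.13, continuity-corrected 7.18. The stated figure is thus the independent-observations value and contains no design effect.

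**Step 2: allow for clustering by physician.**
Design effect DE = 1 + (m − 1) × ICC. Effective n = 200/DE. Half width = 6.93 × √DE.

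| Physicians (assumed) | m | ICC (assumed) | DE | Effective n | Half width (points) |
|---|---|---|---|---|---|
| 40 | 5 | 0.01 | 1 + 4 × 0.01 = 1.04 | 192 | 7.1 |
| 20 | 10 | 0.05 | 1 + 9 × 0.05 = 1.45 | 138 | 8.3 |
| 20 | 10 | 0.10 | 1 + 9 × 0.10 = 1.90 | 105 | 9.6 |
| 10 | 20 | 0.10 | 1 + 19 × 0.10 = 2.90 | 69 | 11.8 |
| 10 | 20 | 0.30 | 1 + 19 × 0.30 = 6.70 | 30 | 17.9 |
| 6 | 33.3 | 0.30 | 1 + 32.3 × 0.30 = 10.7 | 19 | 22.7 |

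**Step 3: where the loss becomes material.** The half width reaches 10 points when DE = (10/6.93)² ≈ 2.08. With 10 physicians this needs an ICC of 1.08/19 ≈ 0.06; with 20 physicians, 1.08/9 ≈ 0.12.

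**Step 4: few clusters.** With few physicians a t critical value on k − 1 degrees of freedom is more appropriate than 1.96. For 10 physicians this gives 13.6 points at ICC 0.10 and 20.7 at ICC 0.30, so the z-based figures in the table are on the favourable side when k is small.

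**The case against.** **The size is unknown.** This stands. The protocol gives neither the number of physicians nor an ICC. A reader might infer from three clinics or wards that only a handful of physicians are involved and that the endpoint is far less precise than claimed. The documents do not support so definite a statement: with 40 physicians and ICC 0.01 the half width is 7.1 points, hardly different from 6.9. Only the direction is firm.

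**The inflation depends on the target of inference.** This also stands, as a condition. If the aim were only to describe uptake by the particular physicians in those clinics, they could be treated as fixed and the design effect would not apply. But the Background describes the study as the first step towards routine assessment across the institute, which implies inference beyond the physicians observed.

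**The analysis plan may handle clustering.** The protocol names no interval method, so a clustered analysis is not ruled out. That does not rescue the precision statement, which is made in this document and expressly covers clinicians.

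**The study is descriptive.** No hypothesis test, success threshold or go/no-go rule hangs on 6.9%. This limits the severity but does not make the figure right.

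Two further readings are tempting but unsupported. A reader might take the 50% as an expected completion rate and conclude that only half of the encounters would have data to open. The protocol uses 50% as a conservative device, and the 200 are enrolled patients, so refusals may largely fall outside them. A reader might also suspect that repeated questionnaires in Studies A and C will be pooled as if independent, for instance in the "average proportion of missing items for each compilation". The main endpoints are at baseline, that average can be taken at each time point, and the protocol does not say that repeated records are pooled.

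**Conclusion.** The point holds in a limited form. The 6.9% half width is correct for patient compliance. For physician compliance in Studies A and B it is too small, given two conditions: some positive within-physician correlation in access, and inference beyond the physicians observed. The first is likely but not documented; the second follows from the project's stated aim. The claim of worst-case precision does not hold for this endpoint under the same conditions.

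The size can be given only as a range under assumptions. The plausible middle of the table runs from about 8 to 18 points, and the full assumed range from 7.1 to 22.7. This should be fixed, because a main endpoint carries a stated precision that its design does not deliver. It does not threaten the study: patient compliance is untouched and no decision rule depends on the figure.

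**What to change.** 1. Limit the 6.9% statement to patient compliance.
2. For physician compliance in Studies A and B, state the expected half width as a range, and give the number of physicians and the ICC behind it, labelled as assumptions. The clinics and wards can supply a realistic count of physicians; the table above can then be narrowed.
3. State that the physician 95% confidence interval allows for clustering by physician, for example by a cluster-robust or GEE interval with a small-sample correction, or by analysing physician-level rates.

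Data collection procedures already provides for automatic registration of clinician access, and Data protection issues for user authentication and access logs. What is needed is that each encounter can be linked to a physician identifier. The cost is wording, that identifier and a less favourable stated precision; no extra patients are required.

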### Methods of qualitative feasibility study

The use of qualitative techniques, namely semi-structured face-to-face interviews and focus groups, is addressed to explore attitudes and opinions about PRMs and ePRMs of both patients and HCPs in the pre-implementation phase, to identify patient and clinician related barriers to adopt ePRM data collection in oncology clinical practice during the feasibility assessment phase (Fig. 1), as well as to pinpoint engagement strategies to promote the use of ePRM system in routine care.

Two separate focus groups (10 patients and 10 clinicians) will be carried out during the pre-development phase of the ePROM system. We opted for two separate focus groups to compare the viewpoints of patients and clinical professionals. After the ePROM feasibility phase, three focus groups, one for each study A, B and C (10 participants each), will also be carried out among clinicians (physicians, psychologists, nurses) who have participated in the three studies. The number of cases in focus groups was determined to support the depth of case-oriented analysis that is fundamental to this mode of inquiry and that would not be possible with wider sample sizes [40], to ensure sufficient heterogeneity between the characteristics of the participants and to allow everyone to intervene in the discussion, avoiding potential frustration due to lack of time to express one’s point of view and opinion [41]. The recruitment strategies will be addressed to ensure heterogeneity with respect to stage of disease (only for patients), professional profiles (only for clinicians) and gender (for both). Thirty semi-structured interviews (enrolling 10 patients for each of study A, B and C) will also be carried out. Purposive sampling will be performed in order to cover a wide range of patient characteristics (sex, age, disease site and stage as well as experience with e-devices and study participation). Feasibility issues addressed during interviews/focus groups will cover aspects common to each study (ease of use of the ePRM, relevance of the content, suggestions for improvement) as well as disease/setting related aspects. A special attention will be dedicated to elderly and to patients with low experience with electronic devices.

Experts in qualitative methods will be engaged both for training and supervision of interviewers that will be enrolled among volunteers and trainees at INT. Data collected will be analysed through T-Lab, a linguistic, statistical and graphical software designed to allow text analysis of qualitative data.

### Post-development phase

The aim of this phase is twofold: to identify specific questionnaires and to develop strategies for the implementation of ePRM systematic assessment in routine oncology care at our Institute (Fig. 1).

A variety of questionnaires are available for the assessment symptom burden, psychological distress, side effects of cancer treatment, experience with care received and quality of life. The choice is to be based on aim of assessment, feasibility and possibility of intervention after assessment. A consensus meeting will be carried out after the feasibility phase is concluded to decide upon which tools to use during the future implementation phase of the PATIENT VOICES project. Representatives of all the clinical and research wards of the INT as well as the research personnel involved in the present project will be invited to participate in the consensus.

Like any change in clinical processes, successful implementation of electronic patient reported assessment in routine clinical workflow, requires institutional commitment from leadership, buy-in from administrators as well as the involvement of multiple stakeholders along the development process. For this reason a multi-disciplinary stakeholder team (MDST) including researchers, oncology clinicians, health informatics professionals, health system administrators and patients will be involved in the development of potentially effective implementation strategies.

The MDST will examine evidence from the literature, results of the survey and of the feasibility studies to answer the following questions:
How, where, and with what frequency will ePRMs be administered?How can users be trained and engaged?How will the ePROM-EMR system interaction be governed?How will ePROM and ePREM data be acted upon?What are the ethical and legal implications of the systematic assessment?

Discussion and consensus among MDST members on the topics above, will be achieved via both meeting participation and written document circulation.

